### Statistical methods

#### Sample size

This pilot RCT is designed as a preliminary to a full-scale confirmatory trial. Therefore, we assume that a total of 50 participants will be an acceptable sample size, considering 20 participants in each group with a 20% drop-out rate.

#### Statistical analysis

Data will be analyzed by an independent statistician who is blinded to the group allocation and who will use the Statistical Package for the Social Sciences (SPSS) Version 23.0 (IBM Inc., New York, NY, USA). The analysis set will consist of the Intent-to-treat (ITT) set, Per-protocol (PP) set, and Full Analysis Set (FAS). The ITT set will include all participants as originally allocated after randomization. The PP set will include the participants who completed three or more treatment sessions (75%) and the entire trial without any major violation of the protocol. Participants who are assessed at least once after random allocation will compose the FAS, which will be used for the main analysis of the treatment outcomes. Safety will be analyzed using the ITT set. The significance level will be set at *p* < 0.05. Missing data will be handled using the last-observation-carried-forward (LOCF) method.

The demographic and baseline characteristics, such as age, gender, medical history, duration of CNP and treatment expectancy, will be summarized for each treatment group. Depending on whether a normal distribution is found or not, baseline assessments for homogeneity will be conducted using the Wilcoxon rank sum test or the *t* test for continuous variables and Fisher’s exact test or the chi-square test for categorical variables.

The primary outcome, the mean changes from baseline to week 6 in the VAS scores, will be compared between the two groups by using the *t* test or analysis of covariance (ANCOVA). If the baseline difference in the VAS score between the two groups is statistically significant, an ANCOVA will be performed with the baseline VAS score as a covariate and the study group as a fixed factor. The paired *t* test or the Wilcoxon signed rank test will be conducted to compare the treatment outcomes before and after intervention in each group. In addition, a repeated-measures analysis of variance (ANOVA) will be used to further confirm the differences in the trends of the visit. The secondary efficacy outcomes will be evaluated using the Wilcoxon rank sum test or the *t* test for continuous variables and Fisher’s exact test or the chi-square test for categorical variables. For safety assessments, all adverse events will be recorded as frequencies with percentages and durations. The chi-square test or Fisher’s exact test will be used to evaluate the statistical significance of between-group differences in the frequencies of adverse events. The duration of each adverse event will be compared between the two groups by using the Wilcoxon rank sum test or the *t* test. Subgroup analyses based on baseline characteristics will also be performed for the primary and the secondary outcomes.

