**Methods/design:**

This study will be an 8-week-long, two-armed, parallel, randomized, subject-assessor-blinded, sham-controlled pilot trial. Fifty eligible patients will be randomly allocated into the real TEA group or the sham TEA group. The real TEA group will receive TEA treatment at 14 fixed acupoints in the neck region. The sham TEA group will receive the same treatment as the real TEA group, but with a sham device with the thread removed. Both groups will receive treatment once a week for a total of four sessions. The primary outcome will be the mean change in the visual analog scale (VAS) from baseline to week 6 (2 weeks post intervention). Clinical relevance (ratio of the number of patients with decreases on the VAS of ≥15 mm or with percentiles ≥ 30% and ≥ 50% relative to baseline to the total number of patients), Neck Disability Index, pressure pain threshold, the Hospital Anxiety and Depression Scale, EuroQol 5-Dimensions questionnaire, Patient Global Impression of Change, blinding test, and adverse events will be used to assess secondary outcomes.

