### Outcome measurement

Outcome measurements will be performed before the treatment (baseline; week 1), 2 weeks after the first treatment (week 3), and 2 weeks (week 6) and 4 weeks (week 8) after the last treatment.

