#### Primary outcome

The primary outcome will be the mean change on the 100-mm VAS from the baseline (week 1) to the primary endpoint (week 6), which will be 2 weeks after the completion of TEA treatment. The 100-mm VAS will be used to assess CNP because it is a fast and straightforward method for evaluating the subjective degree of pain intensity [40]. Participants will be instructed to report the intensity of neck pain experienced within the past week on a linear scale of 0 to 100 (0, no pain; 100, pain as bad as it could be) [41].

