### Pain

The secondary outcome for pain will be the mean change on the 100-mm VAS for CNP from the baseline to week 3, week 6, and week 8, respectively.

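### The per-protocol set requires completion of the whole 8-week trial, so the week-6 per-protocol comparison drops adequately treated participants with an observed week-6 VAS who miss only week 8

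*Protocol article*

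**What the plan says.** The Statistical analysis section names three sets: ITT, PP and FAS. The PP set holds participants who "completed three or more treatment sessions (75%) and the entire trial without any major violation of the protocol". The rule is written once, for all outcomes, with no exception for someone who misses only the last visit.

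The abstract fixes the length of the trial: "This study will be an 8-week-long, two-armed, parallel, randomized, subject-assessor-blinded, sham-controlled pilot trial". Under Outcome measurement, the post-treatment assessments fall "2 weeks (week 6) and 4 weeks (week 8) after the last treatment". Under Primary outcome, the change in VAS runs "from the baseline (week 1) to the primary endpoint (week 6), which will be 2 weeks after the completion of TEA treatment". The week-8 VAS is secondary; the Pain section lists the "mean change on the 100-mm VAS for CNP from the baseline to week 3, week 6, and week 8, respectively".

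The same Statistical analysis section gives the main role to another set: "Participants who are assessed at least once after random allocation will compose the FAS, which will be used for the main analysis". The ITT set serves for safety. On missing values it says: "Missing data will be handled using the last-observation-carried-forward (LOCF) method". No decision or conclusion is attached to the PP result.

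**The concern.** A per-protocol analysis is meant to show the comparison among people who received the treatment adequately and were measured as planned. For the week-6 outcome, everything relevant has happened by week 6: the four weekly sessions ended two weeks earlier, and no study treatment is given between weeks 6 and 8. Attendance at week 8 says nothing about adherence before the primary reading.

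Two things follow from using it as a condition. First, observed primary data are discarded from a set that is already small. Second, membership depends on something that happens after the endpoint and may be a response to it, for instance when a participant does not return because the pain has gone or has not changed. That makes it harder to say what any difference between the PP and FAS results means. Because the pilot is meant to inform a full-scale trial, the definition may also be carried forward.

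**Working it through.** **Inputs**

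- PP rule: at least 3 of 4 sessions, entire trial completed, no major violation (Statistical analysis).
- Trial length 8 weeks (abstract); last assessment at week 8 (Outcome measurement).
- Primary endpoint at week 6 (Primary outcome).
- Sample size: "a total of 50 participants will be an acceptable sample size, considering 20 participants in each group with a 20% drop-out rate" (Sample size).
- Timing of drop-out: not given, so it is varied below.

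**Step 1. Reproduce the planned size.** 20 / (1 − 0.20) = 25 per arm, 50 in total. This matches the article. The planned loss is 0.20 × 25 = 5 per arm, leaving 20 completers per arm.

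**Step 2. Apply the rule to two participants, neither with a major violation.**

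| Participant | Sessions | Week-6 VAS | Week-8 visit | In PP set? | In FAS? |
|---|---|---|---|---|---|
| A | 3 of 4 | observed | attended | yes | yes |
| B | 4 of 4 | observed | missed | no | yes |

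B received more of the treatment than A and has the same primary data, yet B is the one removed. In the FAS, B keeps the observed week-6 value, and carrying the last observation forward touches only B's week-8 value. The main week-6 comparison is therefore the same whether or not B attends week 8.

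**Step 3. Size of the loss.** Assume that the planned 20% is total loss by week 8, that there are no other PP exclusions, and that anyone lost after week 6 otherwise qualifies. Let s be the share of loss falling after week 6. The current rule leaves 20 per arm. A week-6 rule would leave 20 + 5s per arm. With equal arms and an unchanged SD, the standard error under the current rule is larger by √((20 + 5s) / 20).

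| Share of loss after week 6 | Excluded with week-6 data, per arm | Week-6 rule, per arm | SE factor |
|---|---|---|---|
| 0 | 0 | 20 | 1.00 |
| 10% | 0.5 | 20.5 | 1.01 |
| 25% | 1.25 | 21.25 | 1.03 |
| 2/7 (uniform, weeks 1 to 8) | 1.43 | 21.43 | 1.035 |
| 50% | 2.5 | 22.5 | 1.06 |
| 100% | 5 | 25 | 1.12 |

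The uniform case is 5 × (8 − 6) / (8 − 1) = 1.43 per arm.

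**Step 4. What the upper end requires.** Five per arm is reached only if every loss falls after week 6. Losses between the last session (two weeks before week 6) and week 6 have no week-6 VAS, so they do not count. If all losses were spread evenly over weeks 4 to 8, the number would be 5 × (8 − 6) / (8 − 4) = 2.5 per arm, which is the 50% row.

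**The case against.** The strongest reply is that nothing important rests on this set. The FAS carries the main analysis, the PP result triggers no decision, and the trial is a pilot without a power calculation. All of that stands, and it sets the weight of the point.

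A second reply is that requiring completion is a common convention. One PP set serves all outcomes, including the week-8 VAS and global impression of change, and the planned repeated-measures ANOVA across visits naturally uses participants with every visit. This also stands for those analyses. It does not justify the condition for a week-6 comparison, and the change below keeps full completion where it fits.

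A third is that the article is condensed and that a fuller document may define completion or endpoint-specific membership. That would answer an omission, but here a criterion is stated. Completion of the trial is not spelled out as attending week 8, though in an 8-week trial that is its natural reading. If something else was meant, the sentence still needs clarifying.

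Two stronger readings are tempting. A reader might infer that the primary result is weakened; Step 2 shows that it is not. A reader might also infer bias between arms, since only the real arm retains thread (absorbed over about 180 days, per Background) and the article expects post-treatment stiffness and irritation. But the article does not connect these with week-8 attendance, and participants and assessors are to be blinded. Differential selection is possible; the document does not show it.

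**Conclusion.** The point holds as a small improvement to a supportive analysis. As worded, the PP rule removes adequately treated participants with an observed week-6 VAS if they miss only week 8, and it makes membership for the primary outcome depend on a later event.

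Under the Step 3 assumptions, 0 to 5 participants per arm are affected, with a standard-error factor of 1.00 to 1.12 for the week-6 PP comparison. The uniform-loss figure of about 1.4 per arm (factor 1.035) is an illustration, not a forecast, because the article gives no drop-out timing. No direction or size of bias can be stated. The main FAS analysis, the safety analysis and the planned 50 participants are unaffected.

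**What to change.** In the Statistical analysis section, define PP membership by time point. For the week-6 primary outcome: at least three sessions, observed baseline and week-6 VAS, and no major violation up to week 6. Keep the requirement to complete the entire trial only for PP analyses of week-8 outcomes and for all-visit (repeated-measures) PP analyses.

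The cost is about one sentence in the protocol or analysis plan, with no extra visits or participants. The downside is that the PP set may differ slightly in size between time points, so each PP table should state its own number.

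### Safety is analysed by allocated arm rather than by device received, and no set of treated participants is defined for it

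*Protocol article*

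**What the plan says.** The Statistical analysis section defines three sets.

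- **ITT set:** "The ITT set will include all participants as originally allocated after randomization".
- **FAS:** "Participants who are assessed at least once after random allocation will compose the FAS, which will be used for the main analysis" of outcomes.
- **PP set:** participants with at least three of the four sessions who finished the trial without a major violation.

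On safety it says: "Safety will be analyzed using the ITT set". None of the three sets is defined by the treatment a participant actually received. The same section plans a chi-square or Fisher test of adverse event frequencies between groups, and a comparison of event durations. On missing data it says: "Missing data will be handled using the last-observation-carried-forward (LOCF) method".

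Under Sham TEA treatment, the two arms share acupoints, needle sizes and insertion method. The sham participant gets the needling but no thread.

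**The concern.** The safety question in this trial is what the embedded thread adds to needling alone. That is a question about exposure, and the safety set is built on allocation. Two things follow if the text is applied literally.

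- A participant who is randomised but never treated cannot have a treatment-related event, yet counts in the denominator.
- A participant allocated to one device and treated with the other has any event credited to the arm whose device was not used.

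The first lowers the reported rate in that arm. The second pulls the arms together. Dilution towards no difference is a cautious error for efficacy, but for harm it errs on the unsafe side. The pilot is meant to inform a full-scale trial, so an understated rate would be carried forward.

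There is a lesser question on efficacy. The first scheduled outcome assessment after baseline comes two weeks after the first treatment, so a treated participant who leaves before it can fall out of the FAS.

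**Working it through.** **Inputs from the protocol article**

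- Sample size section: "a total of 50 participants will be an acceptable sample size, considering 20 participants in each group with a 20% drop-out rate".
- Design section: equal allocation to two arms.
- Outcome measurement section: first post-baseline assessment at week 3. The Design section labels the same visit week 4; two weeks after a first treatment in week 1 is week 3.
- Randomization and blinding section: randomisation at visit 1, after baseline.
- Not given: the number never treated, the number given the wrong device, adverse event rates, and the timing of drop-out. These are assumed below, with ranges that start at zero.

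**The plan's own figure.** 2 × 20 = 40 evaluable; 40 / (1 − 0.20) = 50 in total, 25 per arm. The stated 50 is reproduced and is not disputed.

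**Untreated participants.** With m of 25 in an arm never treated, true rate p among the treated, and no counted events among the untreated, the ITT rate is p × (25 − m) / 25. For p = 40%:

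- m = 0: 40.0%
- m = 1: 38.4%
- m = 2: 36.8%
- m = 5: 32.0% (every planned drop-out in the arm leaves before any session; an extreme)

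The rate in the affected arm always falls. The between-arm difference falls when untreated participants are spread evenly: with true rates of 60% and 30% and m = 2 in each arm, 55.2% − 27.6% = 27.6 points against a true 30. If both untreated participants were in the sham arm only, the difference would widen: 60% − 27.6% = 32.4 points. Nothing in the design makes that imbalance likely, because participants do not know their allocation.

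**Wrong device.** With c participants in each arm given the other device, and true rates of 60% (thread) and 30% (sham), the difference by allocation is 30 × (1 − 2c/25) points:

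- c = 0: 30.0 points
- c = 1: 27.6 points
- c = 2: 25.2 points

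If the error goes one way only, with one sham participant given thread, the sham rate reads (24 × 30% + 60%) / 25 = 31.2% and the difference is 28.8 points.

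**Efficacy set.** The plan allows for 10 drop-outs. If none, half or all of them leave before the first assessment, the FAS holds 50, 45 or 40 of the 50 randomised. As an illustration, take a mean VAS change of −20 mm among those retained in an arm and 0 among k excluded. The all-randomised mean is −20 × (25 − k) / 25:

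- k = 0: −20.0 mm
- k = 1: −19.2 mm
- k = 2: −18.4 mm
- k = 3: −17.6 mm
- k = 5: −16.0 mm

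**Who is in the FAS.** Membership depends on being assessed, and the text does not say by what. The Blinding assessment section has participants guess their allocation after the first treatment. If that counts, someone who leaves after one session is in the FAS with a baseline VAS only, and carrying the baseline forward would record zero change. If it does not count, the same person is excluded.

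**The case against.** The strongest reply is that the safety error will hardly ever operate. Baseline is in week 1, and week 6 is two weeks after the last of four weekly sessions, so the first session falls in the week of randomisation and few participants can go untreated. One trained, unblinded practitioner treats everyone and can see the thread and anchor, so a wrong device is unlikely. This stands, and it limits the size. It does not make allocation the right basis for a safety analysis. Nor is this an omission that a fuller plan would supply, because the article states the set outright.

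On efficacy, the reply largely succeeds. A full analysis set that requires one post-randomisation assessment is a common modified intention-to-treat choice. A reader might infer that exclusion from it is driven by treatment, since the protocol expects stiffness and irritation after TEA. Both arms receive the same needling, however, and nothing in the document shows that early drop-out would differ by arm. The text also gives the ITT set no efficacy role, but which sets support sensitivity analyses is commonly left to the full plan. An all-randomised analysis would add little information from participants with baseline only, and under missing-at-random assumptions it would not by itself remove bias from tolerability-driven exit.

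**Conclusion.** The safety point holds. The plan assigns safety to a set defined by allocation, while the comparison it wants is between those exposed and not exposed to thread. The expected direction is understatement of harm, provided that untreated participants have no counted events and are not concentrated in the sham arm. The size cannot be derived from the document: it is zero if everyone is treated as allocated. In the illustrations it is about 1.6 points on a 40% rate per untreated participant in an arm of 25, and 2.4 points on a 30-point difference per wrong-device participant in each arm. Given the trial's conduct, the numbers should be small.

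A reader might infer that the two sets have simply been exchanged. They have not. Moving safety to the FAS would not repair the plan, because the FAS is not defined by treatment received and could lose treated participants with no later assessment. A reader might also infer that the main efficacy analysis is invalid. The document does not support that: the FAS is a usual choice with a loosely worded entry rule, and it merits a clarification and a sensitivity analysis.

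**What to change.** Replace the safety sentence with a safety set of all participants who received at least one session, analysed by the device actually received. Add a rule for anyone who received both devices over the four sessions. This needs a record of the device used at each session.

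As a secondary change, make FAS membership depend on at least one post-baseline VAS. Report an all-randomised (ITT) analysis of the primary outcome beside it as a sensitivity analysis, with stated assumptions for participants who have baseline only. The Design and Outcome measurement sections should also agree on the week of the first post-baseline visit.

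The cost is wording and slightly more analysis work. Design, sample size and data collection schedule are unaffected. Any participant given the wrong device would be compared outside the randomised grouping in the safety analysis, which is acceptable when such cases are few and are reported. The changes should be fixed before the allocation is unblinded.

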### Design

This study will be a single-center, equally randomized, two-armed, parallel, stratified (gender), subject-assessor-blinded, sham-controlled pilot trial. This trial is being conducted at the Pain and Spine Center, Dunsan Korean Medicine Hospital of Daejeon University (DKMHDU), Korea.

A total of 50 participants diagnosed with CNP will be recruited from the Clinical Trial Center of DKMHDU in Daejeon through advertisements in local newspapers, on hospital websites and bulletin boards, in information leaflets, etc. The recruitment period will run from May 2017 to December 2017. Clinical research coordinators will interview all potential participants over the telephone and schedule screening visits. At the screening visits, all potential participants will be informed of the objectives and the overall procedure of the trial and will be asked to provide written informed consent. Study volunteers will go through a screening process, which will include radiography of the cervical spine and physical examinations, to verify the diagnosis of non-specific CNP.

At visit 1, an eligible participant will receive baseline assessments, including the use of the acupuncture expectancy scale [30, 31], and will then be randomly allocated into one of two groups: the real TEA group and the sham TEA group. The real TEA group will receive TEA treatment at local acupoints in the neck region. The sham TEA group will receive the same treatment as the real TEA group, but with a sham device with the thread removed. Both groups will receive treatment once a week for a total of four sessions. The real TEA and the sham TEA will be described to the participants as “classical TEA” and “non-classical TEA,” respectively. Researchers will explain to the participants that the term “classical TEA” is “typically used in Korean Medicine clinics” while the term “non-classical TEA” is “rarely used in Korean Medicine clinics” [32, 33]. Outcome measures will be assessed before the treatment (week 1), 2 weeks after the first treatment (week 4), and 2 weeks (week 6) and 4 weeks (week 8) after the last treatment. A flowchart of the study is illustrated in Fig. 1, and the clinical trial schedule is presented in Fig. 2.

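### LOCF in the main analysis replaces a missing week-6 VAS with a mid-course score, which shrinks an effect that is still growing and can bias the comparison either way if drop-out is unequal

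*Protocol article*

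**What the plan says.** All references are to the protocol article.

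- **Missing data** (Statistical analysis): "Missing data will be handled using the last-observation-carried-forward (LOCF) method". The rule is not limited to any outcome or analysis, and no other missing-data method is named.
- **Main analysis set** (Statistical analysis): "Participants who are assessed at least once after random allocation will compose the FAS, which will be used for the main analysis". The only use stated for the ITT set is safety. The per-protocol set requires at least three sessions and completion of the whole trial.
- **Primary endpoint** (Primary outcome): change in the 100-mm VAS from baseline to week 6, which is 2 weeks after the last session. The test is a t test, or ANCOVA if baseline VAS differs significantly, with "The significance level will be set at *p* < 0.05".
- **Visits** (Outcome measurement): baseline, 2 weeks after the first treatment, week 6 and week 8. The second visit is called week 3 there and week 4 in Design.
- **Planned drop-out** (Sample size): "a total of 50 participants will be an acceptable sample size", "considering 20 participants in each group with a 20% drop-out rate".
- **Repeated-measures ANOVA** (Statistical analysis): it "will be used to further confirm the differences in the trends of the visit". It is not described as dealing with missing data.

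**The concern.** LOCF gives the right week-6 mean only if pain does not change after the last visit attended. The protocol expects otherwise. Its Discussion expects dry-needling to relieve pain in both arms, and expects real treatment to be superior because the embedded thread goes on stimulating. Part of the hypothesised benefit therefore comes late, and LOCF removes it from anyone lost after the mid-course visit.

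Two things follow. If drop-out is equal, an effect that is still growing is diluted. If drop-out is unequal, the later improvement shared by both arms is credited more to the arm with fewer drop-outs, and this can happen with no treatment effect at all.

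FAS entry needs only one assessment of any kind. If the allocation-guess questionnaire after the first session qualifies, a participant could enter the main analysis with baseline carried forward, a change of exactly zero.

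The responder rates and the repeated-measures ANOVA fall under the same blanket rule. Efficacy against sham is part of the primary objective, and the result is meant to inform a full-scale trial.

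**Working it through.** **Planned size.** 20 / (1 − 0.20) = 25 per arm, and 2 × 25 = 50, which matches the protocol. The ceiling on imputed week-6 values is 0.20 × 25 = 5 per arm. The actual number is lower if some drop-outs leave the FAS (no later assessment) or are lost only after week 6.

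**Which value is carried.** Sessions are weekly, four in all, and the second assessment is 2 weeks after the first. Under either label (week 3 or week 4) it falls no later than the week of the last session, and at least 2 weeks before the primary endpoint.

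**Expected value under LOCF.** With drop-out share p in an arm and drop-out unrelated to outcome:

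E(LOCF) = (1 − p) × week-6 mean + p × mid-course mean.

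**Equal drop-out, p = 0.20.** If a fraction f of the week-6 effect is present mid-course, LOCF retains (1 − p) + p × f of it:

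| f | Retained |
|---|---|
| 0 | 0.80 |
| 0.5 | 0.90 |
| 0.8 | 0.96 |
| 1 | 1.00 |

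A 15 mm effect with f = 0.5 becomes 13.5 mm. The 15 mm is borrowed for illustration from the within-patient MCID in Clinical relevance; the protocol states no between-group effect. Carrying baseline forward corresponds to f = 0.

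**Unequal drop-out, no true effect.** If both arms improve a further T mm after the mid-course visit, the spurious difference is (difference in p) × T. With 10% against 30% and T = 5, 10 or 15 mm:

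0.20 × 5 = 1 mm; 0.20 × 10 = 2 mm; 0.20 × 15 = 3 mm.

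The sign favours whichever arm loses fewer participants. In simulation (25 per arm, 20,000 replicates, assumed SD 20 mm and mid-course/week-6 correlation 0.6), T = 5 and T = 10 gave biases of 1.0 and 2.0 mm, with rejection rates of 5.3% and 6.1% at the 5% level.

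**Unequal drop-out, true effect 15 mm, f = 0.5, T = 10 mm.** Assume a sham mean change of −10 mid-course and −20 at week 6, and a real mean change of −17.5 and −35.

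- 30% real, 10% sham: real 0.7 × (−35) + 0.3 × (−17.5) = −29.75; sham 0.9 × (−20) + 0.1 × (−10) = −19. The difference is −10.75 mm, so the effect is understated by about 4.2 mm. Simulated 95% CI coverage is 89.5%.
- 10% real, 30% sham: real 0.9 × (−35) + 0.1 × (−17.5) = −33.25; sham 0.7 × (−20) + 0.3 × (−10) = −17. The difference is −16.25 mm, so the effect is overstated by about 1.3 mm.

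**Standard error, 20% missing per arm, SD 20 mm, correlation 0.6 (assumed).** An analysis valid under missing at random (MAR) that uses the mid-course score has

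SE = √[2 × (400/20) × (1 − 0.20 × 0.36)] = √37.12 ≈ 6.09 mm.

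In the simulated 15 mm scenarios with equal drop-out, the LOCF t test reports on average 5.73 mm (T = 5) and 5.85 mm (T = 10). The ratios 5.73/6.09 = 0.94 and 5.85/6.09 = 0.96 give an understatement of roughly 4 to 6%.

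**The case against.** The best defence is scale. This is a 50-participant pilot with no power calculation, and a bias of 1 to 3 mm is small beside a standard error of about 6 mm (assumed SD) and the 15 mm MCID that the protocol cites. That stands, and it sets the severity.

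Several stronger readings are tempting but not supported:

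- *That about 10 of 50 week-6 values will be imputed.* The 20% is overall drop-out in the sample-size allowance. It is a ceiling, because people who leave the FAS or are lost after week 6 need no imputation for the primary endpoint.
- *That the standard error shrinks by 11%.* √(20/25) = 0.894 compares LOCF with discarding drop-outs altogether, not with an analysis that uses their mid-course scores. The t-test error also matches the sampling spread of the LOCF estimate itself (5.85 against 5.84 mm in the simulation with T = 10), so the shortfall is only relative to valid estimation of the week-6 effect.
- *That thread discomfort will produce unequal drop-out.* The protocol mentions stiffness and irritation as a route to guessing allocation and as adverse events, and never links them to drop-out. The 10% against 30% split is an assumption.
- *That LOCF is reliably conservative, or reliably manufactures efficacy.* The sign depends on which arm loses more people and on the time course, which the protocol does not give.
- *That exactly half the course remains at the mid-course visit.* The two week labels conflict, the schedule figure is not shown, and the text does not say whether that day's session comes before or after the assessment.

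The per-protocol set should need little imputation at week 6, but it selects on completing the trial, so it does not correct the problem. A separate analysis plan might add sensitivity analyses. It would not alter the fact that the protocol names LOCF as the method.

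**Conclusion.** The point holds at moderate size. The stated rule scores a missing primary endpoint with a value taken during the treatment course, against the protocol's own expectation of continuing effect. At the planned ceiling of 20% with equal drop-out, and an effect that has not passed its peak by mid-course, LOCF keeps 80 to 100% of the true effect. Bias is nil only if nothing changes after the mid-course visit, or if both arms share the same later trend and drop out equally. Unequal drop-out biases in either direction, by 1 to 3 mm under no true effect in the illustrated range. Understatement of the standard error is secondary. The time course, SD, correlation and drop-out split are all assumptions, since the protocol gives none of them. Should-fix: the trial is a pilot, but it tests efficacy at the 5% level and its estimate is meant to feed a larger trial.

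**What to change.** 1. Make the primary analysis a likelihood-based mixed model for repeated measures on the observed VAS, with treatment, visit, treatment-by-visit and gender (the stratification factor) and an unstructured covariance. Enter baseline VAS either as a covariate or in the outcome vector, not both. Read the week-6 treatment contrast as primary.
2. Analyse participants in the groups to which they were randomised. Those with no post-baseline VAS enter the model only if baseline is in the outcome vector, and they add little information.
3. Use multiple imputation for the responder rates.
4. Keep LOCF only as a sensitivity analysis.
5. Reconcile the week-3 and week-4 labels for the mid-course visit, and state whether a non-VAS assessment is enough for FAS membership.

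Cost: a wording change and slightly more analysis work, with no new data; the named package (SPSS) fits mixed models. The interval may be slightly wider than under LOCF. The model relies on missing at random, which cannot be verified and could fail if people leave for reasons that their recorded scores do not capture.
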